## 11. Safety monitoring

### 11.1. Definition

**Unexpected** events that have not been defined as outcomes (see Section 6.2.1, 6.2.2), expected complications of potassium supplementation, expected complications of CABG surgery or expected complications of usual clinical care (see Section 11.2) should be reported as either a serious adverse event (SAE) or non-serious adverse event (NSAE), depending on their severity. Safety reporting for each patient should commence from time of randomisation to completion of follow-up at 6 months after the CABG surgery.

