The efficacy of the practice of maintaining high-normal serum potassium levels for the prevention of AF after cardiac surgery, however, remains unproven and data supporting it are extremely limited, being derived from observational studies rather than randomised trials. Indeed, no data exist to demonstrate that maintaining a high-normal potassium level is beneficial in these circumstances, or that aggressive replenishment of potassium in these patients improves outcome.

Meanwhile, potassium supplementation may cause discomfort or harm. Routine central venous potassium administration in the early post-operative period, when oral supplementation is not possible, is time-consuming, costly and associated with clinical risk: rapid infusion can prove fatal, and leaving central venous catheters in situ for the sole purpose of potassium replacement increases infection risk. Oral replacement (when feasible) is commonly associated with profound nausea and gastrointestinal side effects, and is very poorly tolerated by patients. The annual costs of intravenous potassium exceed those for other drugs in many cardiac surgical units due to the large quantities administered. Nursing time (e.g. for drug checks and administration) will add to this cost.

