#### 6.1.2. Site and PI responsibilities

- Identify at least one local Principal Investigator (PI)
- Agree to incorporate the Tight K Trial into routine post-surgical and critical care clinical practice
- Adherence with the most recent approved version of the trial protocol
- Ensure training of relevant site staff in accordance with the trial protocol and ICH-GCP requirements
- Agree to randomise all eligible patients and maintain a screening log
- Agree to adhere to individual patient randomisation allocations
- Agree to timely data collection, entry and validation
- Agree to prompt notification of all adverse events

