### **6.2.2. Secondary outcomes**

- Prevalence of all AF, including those identified on holter monitors
- Prevalence of all other non-AF dysrhythmias, defined using standard diagnostic criteria
- In-patient mortality
- 6-month mortality
- Critical care length of stay
- Hospital length of stay
- Costs relating to potassium therapy
- Quality of life at 6 months

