### 11.2. Expected adverse events

- Skin irritation from ECG electrodes
- Hyperkalaemia ( $[K^+] \geq 5.5$  mEq/L)
- Line site complications (phlebitis, infection etc.)
- Nausea
- Constipation, vomiting (due to receiving oral potassium supplementation)
- Myocardial infarction
- Stroke
- Renal failure requiring dialysis
- Renal impairment not requiring dialysis
- Wound infection (sternum or donor site)
- Return to theatre for bleeding
- Prolonged mechanical support
- Post-op delirium
- Non-cardiac chest pain
- Heart failure
- Pleural effusion
- Chest drain insertion
- Pericardial effusion
- Chest infection (pneumonia)
- Lung atelectasis
- Pneumothorax
- Shortness of breath caused by any of the above

- Blood transfusion
- Pericarditis
- Ulnar nerve paraesthesia
- Heart block requiring pacemaker
- Urinary tract infection
- Suprapubic catheter
- Urinary retention
- Intra-aortic balloon pump insertion

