### **11.3. Unexpected Serious Adverse Events**

Any untoward medical occurrence/effect that:

1. Results in death
2. Is life-threatening\*
3. Requires hospitalisation or prolongation of existing hospitalisation
4. Results in persistent or significant disability or incapacity
5. Consists of a congenital anomaly or birth defect
6. Is otherwise considered medically significant by the investigator

\*Life-threatening, in the definition of a SAE, refers to an event in which the patient was at risk of death at the time of event. It does not refer to an event that hypothetically might have caused death if it were more severe.

Unexpected SAEs should be reported to the CTU within 7 days. The report should include an assessment of seriousness and causality (see Section 11.5.2) by the Principal Investigator, or a member of staff delegated this task, at each site.

The Chief Investigator will be responsible for the prompt notification of findings that could adversely affect the health of patients or impact on the conduct of the trial. Notification of confirmed **unexpected** and **related** SAEs will be to the Sponsor, the Research Ethics Committee (REC) and the Data and Safety Monitoring Committee (DSMC).

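### Section 11.1 exempts outcomes and expected complications from adverse event reporting, with no exception for a serious event suspected to be caused by potassium management

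*Protocol*

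**What the plan says.** Section 11.1 confines SAE and NSAE reporting, from randomisation to the end of 6-month follow-up, to unexpected "events that have not been defined as outcomes (see Section 6.2.1, 6.2.2), expected complications of potassium supplementation". It then also excludes expected complications of CABG surgery and of usual care.

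The outcomes in 6.2.2 include "In-patient mortality", mortality at 6 months, and "Prevalence of all other non-AF dysrhythmias, defined using standard diagnostic criteria". The expected events in 11.2 include "Hyperkalaemia", defined by a lower limit of 5.5 mEq/L, with no upper limit and no limit on seriousness.

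The timed duties sit in 11.3 and 11.4. For serious events, "Unexpected SAEs should be reported to the CTU within 7 days", and that report carries the site's assessment of seriousness and causality. Unexpected non-serious events are reported within 14 days, with causality and intensity. Onward notification to the Sponsor, REC and DSMC is for SAEs that are both unexpected and related.

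Two other places pull the opposite way. The first seriousness criterion in 11.3 is "Results in death", and 6.1.2 has sites "Agree to prompt notification of all adverse events".

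**The concern.** The two arms differ in the potassium threshold that triggers supplementation, so the harms most specific to the trial come from potassium that is too high, too low or given too fast. The background in 4.1 acknowledges the hazard of intravenous replacement: "rapid infusion can prove fatal". Yet the serious forms such harm may take (death, dysrhythmia, severe hyperkalaemia) are the ones that 11.1 takes out of reporting, and no clause brings them back when a causal link is suspected.

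At stake is whether anyone at the site has to judge relatedness in the individual case, and by when. A count of deaths or dysrhythmias by arm does not answer that. The conflicting instructions also mean that two sites could handle the same event differently. Because clinical staff know the allocation (8.3.3), reporting left to discretion may also differ between arms.

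**Working it through.** No figure in the protocol bears on this point, so the check is to trace events through the reporting rules.

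**Step 1: which events pass 11.1?** An event is reportable if it is unexpected, is not an outcome (6.2.1, 6.2.2) and is not an expected complication (11.2).

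**Step 2: what follows if it passes?** If serious, a report within 7 days with causality (11.3). If not serious, a report within 14 days with causality and intensity (11.4).

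**Step 3: apply both steps to events suspected to be caused by potassium management.**

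| Event | Outcome? | Listed in 11.2? | Causality assessment and deadline clearly required? |
|---|---|---|---|
| Death up to 6 months | Yes | No | No |
| Life-threatening non-AF dysrhythmia | Yes | No | No |
| Serious hyperkalaemia | No | Yes | No |
| Infusion error, even if fatal | No | No | Yes |
| Serious hypokalaemia | No | No | Yes |

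The first three rows are the gap. The last two rows mark its limit.

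**Step 4: does other text close the first three rows?**

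- Section 8.5 sends malignant dysrhythmias found on Holter to the participant's primary care team, after the event. It names no report to the CTU, Sponsor, REC or DSMC.
- Section 9.3 has adverse events attributed to potassium replacement collated as data. It sets no deadline and no causality scale.
- Section 11.3 makes the Chief Investigator responsible for promptly notifying findings that could harm patients. That depends on the Chief Investigator learning of them, and section 11 requires no site report for an exempt event.
- Section 11.6 provides for urgent safety measures, with immediate notice to the Sponsor and REC. It too presupposes that the hazard is known.

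These routes exist, but none requires a site causality assessment by a set time.

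**Step 5: would the assessment work if it were made?** In 11.5.2 the grades probable and possible are defined by timing relative to an RIC procedure. That term is not in the glossary and no such procedure is part of this trial. As written, even a reported event is not assessed against potassium management.

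**The case against.** The strongest reply is that exempting outcomes and foreseeable complications is a deliberate and reasonable choice in a pragmatic trial of two thresholds for routine care. That stands, and nothing here asks for the exemption to be removed.

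A second reply is that 11.1 and 11.3 do not contradict each other: 11.3 is headed for unexpected events and merely grades those that have passed 11.1. That reading is available, but it confirms that a death counted as an outcome is not graded at all. On the opposite reading, any untoward event meeting an 11.3 criterion is reportable, and the exemption is then empty for serious events. Either way, sites need to be told which applies. The line in 6.1.2 is one bullet in a list of site duties and section 11 is the specific rule, so that is loose wording to be aligned rather than proof of a safety failure.

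A reader might infer three stronger things, which the documents do not support:

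- *That such events get no causality assessment and no expedited report at all.* The text supports only that none is clearly required. The death criterion in 11.3 and the routes in step 4 leave room for a report.
- *That a fatal rapid infusion falls inside the exemption.* The sentence in 4.1 is background. An infusion error is neither an outcome nor on the 11.2 list, so it stays reportable within 7 days even if the patient dies.
- *That these harms would reach the Sponsor and REC only as outcome counts.* Sections 9.3, 11.3 and 11.6 give other routes, if less structured ones. The text of section 14.3 on the DSMC was not available for this review, so whether the DSMC looks at deaths by arm cannot be judged.

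**Conclusion.** The point holds in a limited form. Section 11.1 lacks an exception for a serious outcome or expected event suspected to be caused by potassium management. For such an event, neither a causality assessment nor a timed report is clearly required. Section 6.1.2 is inconsistent with section 11, and the causality scale in 11.5.2 is anchored to the wrong procedure. This rests on a literal reading of 11.1 to 11.5 against the outcome list in 6.2.2.

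The size cannot be given. It is tempting to scale the feasibility study's deaths by 28 days: 2/160 = 1.25% (exact 95% CI 0.15% to 4.44%), times 1684 gives about 21 deaths (about 3 to 75). Those are deaths from all causes and assume that the feasibility rate carries over. They do not measure how many events fall in the gap, because the protocol gives no rate of potassium-related events.

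This is a cheap improvement on a patient-safety matter that the sponsor should make. It does not affect the primary analysis or the sample size.

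**What to change.** 1. Keep the general exemption and add to 11.1: *A death, a life-threatening dysrhythmia, or a serious event listed in 11.2 is reported under 11.3 with a causality assessment when the site suspects that it is possibly or probably related to potassium management in either arm, even though it is an outcome or expected.*
2. In the same place, say whether the onward notification to Sponsor, REC and DSMC applies to these events. Section 11.3 limits that step to SAEs that are both unexpected and related, so otherwise the report could stop at the CTU.
3. Reword the bullet in 6.1.2 so that it refers to the events reportable under section 11.
4. In 11.5.2, replace the RIC procedure with potassium management under the trial protocol. Without this, the assessment required by item 1 would have no valid scale.

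The cost is a few lines of text and a little more reporting work at sites. The number of extra reports cannot be estimated from the documents. The trigger is the suspicion of staff who know the allocation, so the exception does not require a causality assessment of every death, and counts of these reports by arm should be treated as descriptive.

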### 11.2. Expected adverse events

- Skin irritation from ECG electrodes
- Hyperkalaemia ( $[K^+] \geq 5.5$  mEq/L)
- Line site complications (phlebitis, infection etc.)
- Nausea
- Constipation, vomiting (due to receiving oral potassium supplementation)
- Myocardial infarction
- Stroke
- Renal failure requiring dialysis
- Renal impairment not requiring dialysis
- Wound infection (sternum or donor site)
- Return to theatre for bleeding
- Prolonged mechanical support
- Post-op delirium
- Non-cardiac chest pain
- Heart failure
- Pleural effusion
- Chest drain insertion
- Pericardial effusion
- Chest infection (pneumonia)
- Lung atelectasis
- Pneumothorax
- Shortness of breath caused by any of the above

- Blood transfusion
- Pericarditis
- Ulnar nerve paraesthesia
- Heart block requiring pacemaker
- Urinary tract infection
- Suprapubic catheter
- Urinary retention
- Intra-aortic balloon pump insertion

### **11.3. Unexpected Serious Adverse Events**

Any untoward medical occurrence/effect that:

1. Results in death
2. Is life-threatening\*
3. Requires hospitalisation or prolongation of existing hospitalisation
4. Results in persistent or significant disability or incapacity
5. Consists of a congenital anomaly or birth defect
6. Is otherwise considered medically significant by the investigator

\*Life-threatening, in the definition of a SAE, refers to an event in which the patient was at risk of death at the time of event. It does not refer to an event that hypothetically might have caused death if it were more severe.

Unexpected SAEs should be reported to the CTU within 7 days. The report should include an assessment of seriousness and causality (see Section 11.5.2) by the Principal Investigator, or a member of staff delegated this task, at each site.

The Chief Investigator will be responsible for the prompt notification of findings that could adversely affect the health of patients or impact on the conduct of the trial. Notification of confirmed **unexpected** and **related** SAEs will be to the Sponsor, the Research Ethics Committee (REC) and the Data and Safety Monitoring Committee (DSMC).

### **11.4. Unexpected Non-Serious Adverse Events**

Unexpected NSAEs should be evaluated by the PI or a member of staff delegated this task. This should include an assessment of causality (see Section 11.5.2) and intensity (see Section 11.5.1) and reports made within 14 days. The CTU will keep detailed records of all unexpected adverse events reported. Reports will be reviewed by the Chief Investigator to consider intensity, causality and expectedness. As appropriate, these will be reported to the Sponsor, the DSMC and the REC.

### **11.5. Reporting unexpected adverse events**

Investigators will make their reports of all unexpected adverse events, whether serious or not, to the CTU at LSHTM.

#### **11.5.1. Assessment of intensity**

Mild: The patient is aware of the event or symptom, but the event or symptom is easily tolerated.

Moderate: The patient experiences sufficient discomfort to interfere with or reduce his or her usual level of activity.

Severe: Significant impairment of functioning; the patient is unable to carry out usual activities and/or the patient's life is at risk from the event.

#### **11.5.2. Assessment of causality**

Probable: A causal relationship is clinically / biologically highly plausible and there is a plausible time sequence between onset of the adverse event and the RIC procedure.

Possible: A causal relationship is clinically / biologically plausible and there is a plausible time sequence between onset of the adverse event and the RIC procedure.

Unlikely: A causal relationship is improbable and another documented cause of the adverse event is most plausible.

Unrelated: A causal relationship can definitely be excluded and another documented cause of the adverse event is most plausible.

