### **8.3. Randomisation**

Patients who have consented to take part will be allocated using an online randomisation system to receive either 'tight' or 'relaxed' potassium control. Where possible, randomisation should occur on the day of the CABG surgery.

Treatment allocation will be random and in a 1:1 ratio between the two groups. The randomisation allocation sequence will be computer generated using randomly permuted blocks of varying size and stratified by site.

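### Adverse-event causality is timed against an 'RIC procedure' that is not part of this trial, so the relatedness grade used for onward SAE notification is wrong as written

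*Protocol*

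**What the plan says.** Protocol Section 11.5.2 gives four causality grades. The two upper ones, Probable and Possible, differ only in how plausible the causal link is judged to be. Both add the same timing condition, namely that "there is a plausible time sequence between onset of the adverse event and the RIC procedure".

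The two lower grades name no exposure. Unlikely applies when "A causal relationship is improbable and another documented cause of the adverse event is most plausible". Unrelated keeps that second condition but requires the causal link to be ruled out altogether.

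Section 8.3 describes what is randomised: consenting patients "will be allocated using an online randomisation system to receive either 'tight' or 'relaxed' potassium control". Section 8.4 starts trial treatment at admission to ICU or another post-operative facility and ends it at 120 hours, at hospital discharge or at a clinically identified AF episode, whichever comes first.

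Two sections rely on the grades. Section 11.3 requires each unexpected SAE report to carry a causality assessment under Section 11.5.2. It then says that notification of confirmed SAEs that are both unexpected and related goes to three bodies: "SAEs will be to the Sponsor, the Research Ethics Committee (REC) and the Data and Safety Monitoring Committee (DSMC"). For unexpected non-serious events, Section 11.4 says of the site's evaluation: "This should include an assessment of causality (see Section 11.5.2) and intensity (see Section 11.5.1").

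**The concern.** The exposure against which sites must time an adverse event does not exist in this trial. RIC is missing from the glossary in Section 1, plays no part in the treatment described in Sections 8.3 and 8.4, and is not explained elsewhere in the text available. Because the phrase appears intact in two separate definitions, a text-extraction fault is unlikely. It looks like wording carried over from another study, although that is an inference.

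This matters because Section 11.5.2 is an instruction to sites, not background. Its grade is the only stated basis for calling an event related, and relatedness is a condition of the onward notification in Section 11.3. Staff are not blinded to allocation (Section 8.3.3), so the definition should leave little to individual judgement. The trial asks whether giving less potassium is acceptable, so its causality rule must be able to register a harm that follows from not giving it.

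**Working it through.** No arithmetic is needed to test this point. The check sets the sections side by side.

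**1. What each grade requires**

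| Grade | Causal judgement | Reference exposure | Other documented cause needed? |
|---|---|---|---|
| Probable | highly plausible | RIC procedure | no |
| Possible | plausible | RIC procedure | no |
| Unlikely | improbable | none named | yes |
| Unrelated | excluded | none named | yes |

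Two of the four grades name the RIC procedure, and they are the only two that could reasonably support a finding of 'related'. That mapping is an assumption, because Section 11.3 does not say which grades count.

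**2. Literal reading.** No participant undergoes an RIC procedure under this protocol, so the timing condition in Probable and Possible cannot be met. Unlikely and Unrelated remain open only when another documented cause is the most plausible one. An event with no such cause therefore fits no grade. An event that has one and is judged improbable can still be graded Unlikely.

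**3. Substituted readings.** A site that does not read the text literally must choose an exposure. Take a relaxed-arm participant who has received no potassium and has an unexpected event after surgery.

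- *Potassium supplementation*: there is no exposure to time the event against, so Probable and Possible stay out of reach.
- *The CABG surgery*: every post-operative event follows it, so the timing condition is met easily but says nothing about the allocation.
- *The allocated strategy*: the event can be timed against the treatment period and graded.

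The same event can thus receive different grades. The relaxed arm is the more exposed to this. In the feasibility study (Section 4.2), 19 of 79 relaxed-arm patients had a reading below 3.6 mEq/L and so required potassium, which leaves 79 − 19 = 60 who did not. The count is approximate for this trial, because Section 8.3.1 also triggers supplementation at a reading equal to 3.6.

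**4. The time anchor.** Under Section 11.1 safety reporting runs from randomisation to six months after surgery. Trial treatment lasts at most 120 hours from post-operative admission. Reportable events can fall before, during or well after treatment, so what the timing is measured from affects the grade.

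**5. What does not depend on the grade.** Unexpected SAEs go to the CTU within 7 days (Section 11.3), and Section 11.5 sends all unexpected events there, serious or not. Neither step is conditional on causality.

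**The case against.** The strongest reply is that this is a slip that assessors will read through. Most would probably take the phrase to mean the trial treatment, and one who read it literally would meet an obvious gap and query it. Other safeguards also stand outside the definition. The CTU receives every unexpected event. Section 11.3 separately makes the Chief Investigator responsible for prompt notice of findings that could harm patients. The word 'confirmed' in that section suggests a step after the site's grade, and Section 11.4 provides for Chief Investigator review of reports. Urgent safety measures (Section 11.6) and overall safety oversight (Section 11.8) do not turn on Section 11.5.2. AF and other dysrhythmias are trial outcomes, which Section 11.1 keeps out of adverse-event reporting, so the rhythm harms most readily linked to withheld potassium do not reach this definition.

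All of that stands and narrows the consequence. It does not repair the text. Reading the phrase as trial treatment leaves open whether withholding potassium counts as exposure, and central review has no other written definition of relatedness to apply.

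Three stronger inferences are tempting but unsupported.

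- *Sites would class every event as Unlikely or Unrelated, so nothing would be escalated.* Both grades also need another documented cause, and the Chief Investigator's separate duty remains.
- *The feasibility-study share of relaxed-arm patients who needed no potassium measures the events affected.* It counts patients, not adverse events, and the protocol gives no SAE rate.
- *The report forms carry the same error.* They are not shown, so this has to be checked.

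**Conclusion.** The point holds as a should-fix correction to an operative safety rule. The two grades that could make an event related refer to a procedure outside this trial. Taken literally they cannot be met, and some events then have no grade. Taken loosely they allow inconsistent grading, with the greater ambiguity in the relaxed arm.

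The effect is confined to the relatedness grade and the notification that depends on it. First-line reporting to the CTU, the sample size and the primary analysis are unaffected. No numerical size can be given, because the documents hold no rate of unexpected SAEs.

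The conclusion assumes that Probable and Possible are the grades meant by 'related', and that no text outside what was available defines RIC. The text of Section 14 on management and oversight was not available, so what else reaches the DSMC cannot be judged here. A reader might infer that safety oversight as a whole has failed; the independent reporting routes do not support that.

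**What to change.** 1. In both the Probable and Possible definitions, replace 'the RIC procedure' with 'the allocated potassium-maintenance strategy (giving or withholding potassium supplementation)'.
2. State in Section 11.3 or 11.5.2 which of the four grades count as related for onward notification.
3. Check whether the SAE and NSAE report forms carry the same wording, and correct them if they do.
4. Notify sites of the change.
5. Re-check the causality grade of any event already classified.

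The cost is a wording amendment, a short site memo and, if events have already been graded, a limited re-review. A form change is needed only if step 3 finds the same phrase. No dose, treatment threshold or analysis changes.
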